### Process evaluation

Our aim is to assess the acceptability, feasibility and fidelity of the peer delivery model in each arm in facilitating linkage to care. We compare the pattern of recruitment per arm and assess the proportion of hard-to-reach AGYW (aged 18 to 24 years) — defined as out of school, recently migrated and those who live in remote areas linked to care in the three study arms. We will also explore potential unintended consequences and ethical issues that arise during peer referral and HIVST and ascertain what works for whom and when to be able to modify the intervention to improve equitable reach and coverage. Specifically, we will explore the reach of network recruitment compared with peer outreach work, in terms of reaching more vulnerable groups (out of school, recently migrated and those who live more remotely). Entrenched in realist evaluation, this process evaluation uses a mixed method approach (quantitative and qualitative research techniques) to investigate implementation, mechanisms of impact and contextual factors, informed by the UK medical research council guide^43^ and wider implementation science literature with a focus on fidelity, reach and acceptability.^44^

### Cost-effectiveness evaluation

We compare the costs in intervention and control arms. Cost per case linked to PrEP eligibility assessment (HIV-negative) and cost per case started on ART (HIV-positive). To establish costs, we are using both a bottom-up ingredient-based costing approach and a top-down costing approach using the study budgets and expenditure reports. Specifically, we calculate and cost the actual time spent by peer-navigators in each arm for each person linked to care and prevention.

### Data collection

#### Participant survey and clinic linkage

A short survey (service recipient questionnaire) is administered to consenting individuals participating in the study. The questionnaire collects data on participant’s demographic information and coupon identification. The data is captured on REDCap on a tablet. The survey takes approximately 5 min to complete and is administered in both English and isiZulu. The primary outcome of linkage is measured through identifying the consenting eligible young women who link to care through the 11 PHCs and the mobile clinics. We use an algorithm to identify which arm the individual came from, including the barcode on the referral slip they bring, the colour of the referral slips or HIVST pack, their area of residence and the identity of the peer-navigator that recruited them.

#### Programmatic data

In addition to the survey, we collect the programme data records from the peer navigators daily reporting of their outreach activities. This includes the number of young people they have counselled and the numbers they have referred to services and the brief service recipient data they have collected on those who have received referral slips or HIVST packs. We use the programme data in an aggregate way (disaggregated only by gender) to understand the reach and coverage of the programme and compare that with those who link to care. We also use data on changes in self-reported HIVST and linkage services collected through the population intervention surveillance platform.

#### Participant in-depth interviews

In-depth interviews (IDIs) are being conducted with the peer navigators (n=30), clinical team (n=6) stationed in clinics in the participating communities and a purposive sample of young women aged 18 to 24 years (including young men n=45; 30 females (10 per arm), 15 males (five per arm)) across the three arms and clinics. The interviews are conducted by trained social scientists fluent in English and isiZulu and take approximately 60 min in length depending on the participant’s responses, and this enables the researchers to understand, contextualise and explore participants perceptions of the study and some of the issues emanating from the trial. The small number of IDI participants in qualitative study is allowed since deeper meanings of concepts and thematic areas are explored. To limit disturbances and ensure privacy, the IDIs are conducted in a private space suitable for the participant, and audio recorded with interviewees’ consents. Prior to the interview, participants are encouraged to use pseudo names instead of their real names.

### Statistical analysis

The analysis of primary outcome follows an intention-to-treat (ITT) and per-protocol approaches. The primary outcome compares the difference between the rate of linkage of 18- to 24-year-old women to HIV confirmatory HIV testing, ART (if HIV-positive) or PrEP counselling (if HIV-negative). The rate is defined as the number of linkages per month of peer navigator outreach activities. The numerator is defined as the number of young women aged 18 to 24 who attend clinic for confirmatory HIV testing, PrEP counselling or ART, following HIVST distribution or peer navigator referral to HIV testing, treatment and prevention services. The denominator for ITT analysis is the entire time (study duration) spent by peer navigators doing their peer outreach work. For the on-treatment analysis, we will use the actual time spent by peer navigators on distributing packs in each arm. The time worked by each peer navigator will be combined to get the total time per pair of peer navigator. The difference in rate of linkage between the study arms will be calculated — incentivised HIVST delivery through peer network and direct distribution of HIVST will be compared with standard of care.

Since we randomised the pairs of peer navigator (clusters), the rate of linkage will be calculated for each pair of peer navigator using aggregate data for each cluster. Since the number of clusters are small, the effect of the intervention will be estimated using a two-stage approach based on cluster-level summaries.^45^ The cluster-level approach, although less statistically efficient than methods based on individual level regression, is more robust when there are a relatively small number of clusters. All analyses will be performed using Stata V.15 (StataCorp LP, College Station, Texas, USA).

Cluster-level linkage rates will be calculated and used to estimate the unadjusted rate ratio and its 95% CI for the effect of each intervention arm compared with the standard of care; the mean difference in linkage rates between each arm and standard of care, and against each-other will be assessed using a t-test. A rate ratio adjusting for substantial covariate imbalance at baseline will also be calculated, using a two-stage process; all covariates will be prespecified in the analysis plan. To identify covariates for adjustment, baseline characteristics of each arm will be presented, and the size of the difference of covariates known to be associated with the outcome will be assessed quantitatively.

As part of the exploratory analysis, we will perform a (i) subgroup analysis by gender and area and (ii) two intervention arms will be compared with one another (incentivised HIVST delivery through peer network approach will also be compared with direct distribution of HIVST approach). To expand on this, the data from the client survey captured on REDCap dashboard will be exported into Stata, cleaned and analysed. All reporting will conform to Consolidated Standards of Reporting Trials guidance for cluster randomised trials.^44 45^

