**Methods and analysis:**

A three-arm cRCT started mid-March 2019, in 24 areas in rural KwaZulu-Natal. Twenty-four pairs of peer navigators working with ~12 000 young people aged 18 to 30 years over a period of 6 months were randomised to: (1) *incentivised-peer-networks:* peer-navigators recruited participants ‘seeds’ to distribute up to five HIVST packs and HIV prevention information to peers within their social networks. Seeds receive an incentive (20 Rand = US$1.5) for each respondent who contacts a peer-navigator for additional HIVST packs to distribute; (2) *peer-navigator-distribution:* peer-navigators distribute HIVST packs and information directly to young people; (3) *standard of care:* peer-navigators distribute referral slips and information. All arms promote sexual health information and provide barcoded clinic referral slips to facilitate linkage to HIV testing, prevention and care services. The primary outcome is the difference in linkage rate between arms, defined as the number of women (18 to 24 years) per peer-navigators month of outreach work (/pnm) who linked to clinic-based PrEP eligibility screening or started antiretroviral, based on HIV-status, within 90 days of receiving the clinic referral slip.

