Here, we describe a cluster randomised controlled trial to address this critical gap in HIVST evidence and linkage for young women aged 18 to 24 years. Although all young people aged 18 to 30 years are included in the peer-led community based promotion of HIV testing and linkage to HIV prevention and care, the aim of this trial is to determine whether HIVST delivered by peers either directly or through incentivised peer-networks, can increase the uptake of ART and PrEP among adolescent girls and young women (18 to 24 years) in a high HIV transmission setting in KwaZulu-Natal, South Africa. To the best of our knowledge, this is one of the first trials to test the effectiveness of oral-based HIVST to improve uptake of prevention in South Africa.

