#### Primary outcome

The primary outcome compares the difference in linkage rate between arms, defined as the number of women (18 to 24 years) per peer-navigator month of outreach work (/pnm) who linked to clinic-based PrEP eligibility screening or started ART, based on HIV-status, within 90 days of referral.

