**Figure 3 F3:**
[figure not shown]
Peer navigators community outreach workflow. GPS, Global Positioning System; PrEP, pre-exposure prophylaxis; REDCap, Research Electronic Data Capture; VMMC, voluntary medical male circumcision.

Intervention arm 2 - peer navigator direct distribution of HIVST: n=8 pairs of peer navigators are distributing HIVST packs with health promotion and linkage information (eg, clinical referral slips and information about HIV and PrEP) directly to young people aged 18 to 30 years over a period of 6 months. Each person contacted fills a brief *service recipient questionnaire* — self-filled on a tablet. Following which they receive verbal health promotion from the peer-navigator on the HIV prevention services available, the importance of sexual health, the benefits of HIV testing, PrEP and ART and a demonstration of HIV self-screening. All participants are asked to complete a brief check of their understanding of the information provided to them, particularly information about the unreliability of HIVST if someone is on ART, the window period, the recommended support to those under 18 using HIVST and the need for confirmatory testing.

Control arm 3: n=8 pairs of peer navigators are currently distributing packs with health promotion and linkage information (eg, clinical referral slips and information about HIV and PrEP) to encourage young people aged 18 to 30 years to test for HIV at clinics, and link to services/care. Each female aged 18 to 30 approached fills a brief service *recipient questionnaire* — self-filled on a tablet. Following which they receive verbal health promotion from the peer-navigator on the HIV prevention services available, the importance of sexual health, the benefits of HIV testing PrEP and ART.

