**Figure 4 F4:**
[figure not shown]
Mobile/fixed clinics service workflow. ART, antiretroviral; BSID, Bayley Scales of Infant Development; DoH, Department of Health; PrEP, pre-exposure prophylaxis; REDCap, Research Electronic Data Capture; SA_ID, South Africa national identification number; STI, sexually transmittedinfection.

Clinical procedures: Irrespective of whether they consent to the study, all eligible individuals attending clinics are offered confirmatory HIV testing, with two point of care tests and then blood sent to laboratories for ELISA testing (**Genscreen** ULTRA HIV Ag-Ab qualitative immunoassay (fourth Generation) Bio-Rad, Marnes-la-Coquette, France). Individuals who test HIV-negative receive counselling around the benefits of PrEP and HIV-positive individuals receive counselling around the benefits of immediate starting of ART. If they agree, they will undergo clinical screening for PrEP and ART. Screening includes Point of Care tests for creatinine (StatSensor-I create-test strips, Nova Biomedical UK) to assess renal function and hepatitis B (Alere Determine HBsAg, Alere International Limited, Ballybrit, Galway, Ireland; Architect i2000 analyzer, Abbott Diagnostics, Abbott Park, Illinois, USA), with vaccination offered to those who are negative, and sexual behaviour questionnaire to assess eligibility.

If HIV positive, ART is started by the professional nurses in any of 11 PHCs in the study sites. Patients who are eligible for PrEP are started in the three PrEP providing clinics (the mobile vans or the fixed urban adolescent and youth friendly clinic). Persons who are not eligible for PrEP receive counselling and, as indicated, a clinic referral with the screening results. A professional nurse initiates PrEP or ART usually on the same day or within 2 weeks of the screening visit. The professional nurse provides PrEP counselling that includes (1) *sexual health promotion,* with an emphasis on tackling the multiple health-related behaviours that will affect fertility and sexual pleasure (sexually transmitted infections, mental health, alcohol, diet and exercise); (2) assessment of fertility desire and contraception counselling; (3) choice of contraception and condoms; (4) HIV-negative men are also counselled around the benefits of VMMC and referred accordingly.

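### The primary outcome has two different numerators: PrEP eligibility screening or ART start within 90 days in the outcome definition, clinic attendance for testing, counselling or ART in the analysis section

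*Protocol article*

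**What the plan says.** All references are to the protocol article.

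- **Primary outcome section:** the rate counts women aged 18 to 24 "who linked to clinic-based PrEP eligibility screening or started ART, based on HIV-status, within 90 days of referral".
- **Abstract (Methods and analysis):** the same event, but with a different start to the clock: "who linked to clinic-based PrEP eligibility screening or started antiretroviral, based on HIV-status, within 90 days of receiving the clinic referral slip".
- **Cost-effectiveness evaluation:** costs are per HIV-negative case linked to PrEP eligibility assessment and per HIV-positive case started on ART, which are the same events.
- **Statistical analysis section:** the primary outcome is restated as the "rate of linkage of 18- to 24-year-old women to HIV confirmatory HIV testing, ART (if HIV-positive) or PrEP counselling (if HIV-negative". The numerator is then the "number of young women aged 18 to 24 who attend clinic for confirmatory HIV testing, PrEP counselling or ART". No time window is given there.
- **Study recruitment and procedures (clinical procedures):** "all eligible individuals attending clinics are offered confirmatory HIV testing". Counselling follows the test result. Then: "If they agree, they will undergo clinical screening for PrEP and ART".
- **Sample size calculations:** the calculation uses the primary outcome, described as linkage after 90 days, without saying which clinic event counts as linkage.

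**The concern.** A primary outcome needs one numerator. Here the section that defines the outcome and the section that says how to analyse it name different clinic events, and nothing in the article reconciles them. An analyst who follows the Statistical analysis section as written would report a different quantity from the one defined in the Primary outcome section and the Abstract.

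Two things are at stake. The first is the effect estimate: the broader count adds women who stop at testing or counselling, and if they are not equally frequent in the three arms the rate ratio changes. The second is prespecification: with two published numerators, the choice could be made once data are in view, and the Outcomes section plans an interim analysis of this outcome at 3 months.

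**Working it through.** The point disputes no stated figure, so there is none to reproduce. The check sets the definitions against the clinic pathway and then asks when they give the same rate ratio.

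**Step 1. Who counts under each definition.**

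| Woman aged 18 to 24, referred | Primary outcome section | Statistical analysis section |
|---|---|---|
| HIV-negative, screened for PrEP within 90 days | counts | counts |
| HIV-positive, starts ART within 90 days | counts | counts |
| HIV-positive at the clinic test, does not start ART | does not count | counts |
| HIV-negative, counselled, declines screening | does not count, if linkage means screening done | counts |
| Reaches screening or ART start only after day 90 | does not count | counts, unless the window is read in |

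The third row does not depend on how loosely linkage is read: starting ART cannot mean attending.

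**Step 2. Relation between the two rate ratios.** Let *s* be the share of an arm's counted attendees who reach screening or ART start. The outcome-definition count is *s* times the attendance count, so the attendance count is larger by a factor 1/*s*: 1/0.9 = 1.1 at *s* = 0.9 and 1/0.5 = 2.0 at *s* = 0.5. With *s*₀ for control and *s*₁ for an HIVST arm,

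RR(attendance) = RR(outcome definition) × *s*₀ / *s*₁.

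The two agree only if *s*₀ = *s*₁.

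**Step 3. Illustration.** The article gives no value of *s* for any arm, so every share below is an assumption. Write *a* = 1 − *s*₀ and *b* = 1 − *s*₁ for the shares who stop at testing or counselling, and start from a ratio of 2.0 on the outcome definition: RR(attendance) = 2.0 × (1 − *a*)/(1 − *b*).

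| *a* (control) | *b* (HIVST arm) | RR(attendance) |
|---|---|---|
| 10% | 5% | 1.80/0.95 = 1.89 |
| 30% | 10% | 1.40/0.90 = 1.56 |
| 50% | 20% | 1.00/0.80 = 1.25 |
| 5% | 10% | 1.90/0.90 = 2.11 |
| 10% | 30% | 1.80/0.70 = 2.57 |
| 20% | 50% | 1.60/0.50 = 3.20 |

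The last three rows are the first three with the arms swapped.

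**Step 4. Why a few women matter.** The Sample size calculations section plans on 1 woman per 6 months in control against 2, with 8 clusters per arm. Read per cluster, that is 8 against 16 events. Three test-only visits added to control alone give 16/11 = 1.45; three added to the HIVST arm alone give 19/8 = 2.38. Read per navigator (two per cluster), the totals are 16 against 32, and the same additions give 32/19 = 1.68 and 35/16 = 2.19. These are ratios of arm totals with equal outreach time, a simplification of the planned cluster-level analysis.

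**The case against.** **The direction of bias.** A reader might infer that the attendance count selectively inflates the control rate and pulls the ratio towards the null. On that view control slips ask for a clinic test, while women with a self-test kit come only for PrEP or ART. The control-arm description does say its packs are meant "to encourage young people aged 18 to 30 years to test for HIV at clinics", but the same sentence goes on to linkage to services and care. All three arms give slips that promote testing, prevention and care. Participants in both HIVST arms are checked on their understanding that a confirmatory test is needed, and the clinic offers that test to every eligible attendee whatever the arm. Test-only visits could be as common in the HIVST arms or more so, and the second half of the table shows the ratio then rising. The inference is not supported.

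**The 90-day window.** The Statistical analysis section is silent on it; it does not contradict it. The Abstract, the Primary outcome section and the sample size section all state 90 days. The real conflict is in the qualifying event.

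**The uptake aim.** The Introduction asks whether the intervention "can increase the uptake of ART and PrEP among adolescent girls and young women (18 to 24 years". A reader might conclude that the primary outcome misses the trial's aim, since neither numerator requires PrEP to be started. But the second specific aim is the rate of linkage, ART start is itself ART uptake, and uptake of ART and PrEP in the surveillance area is already listed as a secondary outcome.

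**Blinding and the unseen analysis plan.** The statistician is to stay blinded until the results are final, which lessens the risk of a data-driven choice but does not settle which numerator applies. Nor is this a detail properly left to a separate analysis plan, because the article itself states both versions.

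**Conclusion.** The inconsistency stands and concerns the primary outcome, so it must be resolved. The Primary outcome section, the Abstract and the costing section agree on PrEP eligibility screening or ART start; the Statistical analysis section is the outlier.

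The effect on the result cannot be sized from the article. It is nil if the share of attendees going on to screening or ART start is the same in every arm. Otherwise it can go either way: from a ratio of 2.0, the assumed shares give 1.25 to 3.20. That range only illustrates sensitivity; it is not an estimate.

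The conclusion rests on reading linkage to screening as screening done. Under a looser reading the HIV-negative rows come closer together, but the conflict for HIV-positive women who do not start ART remains.

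**What to change.** - In the Statistical analysis section, replace both the restated outcome and the numerator with the event in the Primary outcome section: PrEP eligibility screening done, or ART started, according to HIV status, within 90 days. Do this before the 3-month interim analysis.
- State one time origin for all arms. The Abstract counts from receipt of the slip and the Primary outcome section from referral. These can differ in the network arm, where kits are scanned when handed over for further distribution. A common calendar cut-off 90 days after outreach ends would not do: with 6 months of outreach, a woman referred in the first month would have roughly 8 to 9 months to link, which replaces the 90-day window.
- Report attendance for testing or counselling as a secondary outcome.

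The cost is mainly wording. The article does not show that screening completion and ART start are recorded with dates on the study forms, and ART may be started at any of the 11 primary healthcare clinics, so data capture should be confirmed. The statistical price is fewer events, and so somewhat less precision, than under the attendance count.

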### Qualitative analysis

NVivo software will be used for categorisation and coding of emerging themes from the interview transcripts. Identified themes (including participants’ quotes) and interview transcripts will be reviewed and compared by the research team for inconsistencies and adequate representation of participants’ views. Emerging themes that address the key focus of the study will be examined and analysed following an interpretivist approach.^46^

### Adverse events reporting

HIV testing, including HIVST, is well established and known to have a high level of safety. However, harmful reactions can occur. Adverse events (AE) related to HIVST include all undesirable experiences that result directly from use of the HIVST kit itself or as a reaction from others due to the presence of the kit, use of the kit or results produced from the kit. AEs can be from one person to another, or a person to themselves, and can occur before, during or after self-testing. We rely on participants to report any AEs to the study staff or through the hotline provided on the referral slip. Also, during PrEP resupply and monitoring visits, participants complete a standardised symptom screening questionnaire for adverse effects of PrEP as per South African clinical guidelines. Furthermore, all participants will receive regular creatinine tests to monitor their renal function. Participants who have severe (grade 3/4) adverse effects and serious adverse effects, are referred to the study clinician for medical evaluation. All participants who experience adverse events receive follow-up until the adverse event is resolved.

AEs and serious adverse events (SAEs) are captured through the process evaluation and community engagement units and the telephone hotline. In addition, peer navigators and clinic staff log AEs using our incident reporting form for up to 12 months after the start of the intervention. Reported AEs and SAEs are monitored, categorised based on an established grading system. SAEs are logged, with the Principal Investigator to evaluate the SAE for seriousness and likely relationship to the intervention. Related SAEs are reported to University of KwaZulu-Natal (UKZN) and London School of Hygiene and Tropical Medicine (LSHTM) Ethics Review Boards. All SAEs are reported regularly through 6 month progress reports to TAG members, local and international collaborators. Annual reports with full listings of SAEs will be submitted to Ethics Review Boards.

